## Abstract

**Background:**

Intervention programs with the aim of enhancing parenting quality have been found to be differentially effective in decreasing negative child outcomes such as externalizing behavioral problems, resulting in modest overall effect sizes. Here we present the protocol for a randomized controlled trial to examine the efficacy of the Video-feedback Intervention to promote Positive Parenting and Sensitive Discipline for Twin Families (VIPP-Twins) on parenting quality and children’s behavioral control and social competence. In addition, we aim to test the differential susceptibility theory; we examine differential efficacy of the intervention based on genetic make-up or temperament for both parents and children. Lastly, we explore neurobiological mechanisms underlying intervention effects on children’s developmental outcomes.

**Methods/design:**

The original VIPP-SD was adapted for use in families with twins. The VIPP-Twins consists of five biweekly sessions in which the families are visited at home, parent-child interactions are videotaped and parents receive positive feedback on selected video fragments. Families (*N* = 225) with a same sex twin (mean age = 3.6 years) were recruited to participate in the study. The study consists of four assessments. After two baseline assessments in year 1 and year 2, a random 40 % of the sample will receive the VIPP-Twins program. The first post-test assessment will be carried out one month after the intervention and there will be a long term follow-up assessment two years after the intervention. Measures include observational assessments of parenting and children’s social competence and behavioral control, and neurobiological assessments (i.e., hormonal functioning and neural (re-)activity).

**Discussion:**

Results of the study will provide insights in the efficacy of the VIPP-Twins and reveal moderators and mediators of program efficacy. Overall the randomized controlled trial is an experimental test of the differential susceptibility theory.

**Trial registration:**

Dutch Trial Register: NTR5312; Date registered: July 20, 2015.

**Electronic supplementary material:**

The online version of this article (doi:10.1186/s40359-016-0139-y) contains supplementary material, which is available to authorized users.

## Background

Parenting quality affects a wide array of social, emotional and cognitive child outcomes (e.g., [1, 2]), and intervention programs with the aim of enhancing parenting quality have been found to be effective in decreasing negative child outcomes such as externalizing behavioral problems (e.g., [3, 4]). However, intervention programs may not be equally effective for all families. Such individual differences between individuals in intervention efficacy result in modest overall effect sizes, as have been found for parenting intervention programs [5, 6]. The intervention effects on susceptible families may remain hidden when only overall effects are taken into account. In the current randomized controlled trial (RCT) we examine the efficacy of the Video feedback Intervention to promote Positive Parenting and Sensitive Discipline for Twin Families (VIPP-Twins) on parenting quality and children’s behavioral control and social competence. In addition, we examine markers of differential susceptibility that may be characterizing parents and children who are most open to the positive influences of the intervention program, and on possible neurobiological mechanisms of intervention effects on children’s developmental outcomes.

### Differential intervention effects

Differences in intervention efficacy may be explained by the differential susceptibility model [6–8]. According to this model, not all individuals are equally affected by their environment, and this difference in susceptibility is for better and for worse: Some individuals are more susceptible to both the adverse effects of negative environments and to the positive effects of a supportive environment than others. Moderators of the environmental effects are referred to as susceptibility markers. In the context of parenting, children’s dopamine related gene polymorphisms have been found to be susceptibility factors. For example, Knafo, Israel & Ebstein [9] found a relation between positive parenting and children’s prosocial behavior, but only for children with the DRD4 7-repeat allele. Children with the 7-repeat allele showed the most prosocial behavior when in a positive parenting environment, whereas children with the 7-repeat allele experiencing less positive parenting showed the least prosocial behavior. In addition, evidence for children’s differential susceptibility to a parenting intervention dependent on their genetic make-up was found in a randomized controlled trial [10]: Only children with the DRD4 7-repeat allele showed decreased daily cortisol production and decreased externalizing behavior at two years follow-up.

Kim and Kochanska [11] reported differential susceptibility to parenting with children’s temperament, or negative emotionality, as susceptibility marker. Infants with high negative emotionality developed the highest levels of effortful control and self-regulatory compliance toward their mothers in positive mother-child relationships, but the lowest levels in negative mother-child relationships. Mother-child relationship quality did not affect effortful control of self-regulation for children with low negative emotionality. Similar results were found for childcare quality as environmental factor and behavioral problems as outcome [12]; children with high negative emotionality were more affected by childcare quality, for better and for worse. Gene-by-environment interactions may also be involved in environmental effects on parenting. Parents with so called susceptibility genes were found to be less sensitive in the case of negative environments characterized by early childhood maltreatment, depression and/or daily (parenting) stressors, whereas they displayed the highest levels of sensitivity in positive, supportive environments [13, 14].

An important limitation of these studies is their correlational design. In correlational studies, the environment and the susceptibility marker may be correlated; children’s genetic make-up and their parenting environment may at least partly be caused by the same underlying factor, their parents’ genes [15]. Such gene-environment correlations make it impossible to examine the true moderating effect of heritable child characteristics in the relation between parenting environment and child outcomes. In the current study, we break the gene-environment correlation by using a randomized controlled trial with experimental manipulation of the parenting environment. Experimental manipulation is supposed to lead to positive changes in the family interactions and relationships, in particular in those parents and children who are more susceptible to the environment and profit more from the intervention whereas more susceptible individuals in control group families experiencing (mild) setbacks, conflicts or adversities may suffer more than their less susceptible counterparts.

### Causal mechanisms for change

Most intervention studies have examined the effect on child outcomes of a change for the better in the environment without addressing the question how improvement of the child’s environment results in more adaptive development. To unravel the mechanisms of change, we need to study intervention effects at different levels of functioning [16]. For example, parenting interventions may result in a more normative cortisol regulation over the day in children with negative childhood experiences such as parental separation or child maltreatment [17, 18], or in children with elevated levels of externalizing behavior symptoms [10]. Such neurobiological changes as a consequence of the changed environment might for example explain the persistence of intervention effects over time. In the current RCT, we examine changes at the behavioral, hormonal, and neural level to test for causal mechanisms underlying children’s more adaptive behavioral control and increased social competence after an intervention aimed at increasing supportive parenting behavior.

### VIPP-Twins

The Video-feedback Intervention to promote Positive Parenting and Sensitive Discipline (VIPP-SD) is an attachment based intervention that aims at enhancing parental sensitivity and sensitive discipline [19]. Previous randomized controlled trials have indicated the efficacy of the intervention program in a variety of samples and countries (for an overview, see [20]). A recent meta-analysis indicated an overall combined effect size of d = 0.47 on parental sensitivity [20]. VIPP-SD enhances parental sensitivity, decreases children’s insecure and disorganized attachment, and reduces children’s internalizing and externalizing behavior problems. The VIPP-SD has also been found effective in home-based and center-based child care (VIPP-CC; [21, 22]). In contrast to the VIPP-SD in family settings, the VIPP-CC focusses on sensitive caregiving behavior towards multiple children at the same time. The RCTs in child care indicated increased caregiver sensitivity and more positive caregiver attitudes towards sensitive caregiving and limit setting.

For the current study, we adapted the VIPP-SD protocol for use in families with twins (VIPP-Twins). Parents with twins are an important target group for parenting interventions, because compared to parents of singletons they have additional parenting difficulties. Higher financial and medical stressors and greater parenting demands, such as dividing their attention between two same aged children, put parents of twins at increased risk for mental health problems (see [23] for a review). Furthermore, as the parent is the target of the intervention, we will be able to examine any differential intervention effect between siblings within the same family across pre- to posttest, dependent on genetic dissimilarity in particular of the dopamine-related genetic pathways or in temperamental reactivity. Lastly, the inclusion of monozygotic and dizygotic twins will provide the possibility of genetic modeling of intervention effects.

### Aims and hypotheses

1) The primary aim of the Leiden Consortium on Individual Development (L-CID) is to study the effect of the VIPP-Twins on parental sensitivity and sensitive discipline of the primary parent, one month after the intervention and two years after the intervention (see Fig. 1 for an overview of the different aims). It is expected that sensitivity and sensitive discipline of parents in the intervention condition will significantly increase post-intervention, compared to sensitivity and sensitive discipline of parents in the control condition, who have a similar number of (‘dummy’) contacts with the interveners. 2) The secondary aim is to examine the efficacy of the intervention in enhancing children’s levels of behavioral control and social competence, through increased parental sensitivity and sensitive discipline. 3) A tertiary aim is to test what works for whom by testing the differential susceptibility theory using temperamental reactivity and dopamine-related genotype as main susceptibility markers. We will examine whether the intervention effects on parental sensitivity and sensitive discipline are moderated by parents’ sensory sensitivity [24]) and genotype (dopamine related genetic pathways). 4) More exploratory, we will examine whether the intervention effect on children’s behavioral control and social competence is moderated by children’s genotype (dopamine related pathways) and/or by their reactive temperament, two markers of differential susceptibility that might overlap only partially and thus may have independent moderator effects. 5) Moreover, we aim to explore mediators of change in child outcomes by examining the intervention effect on changes in children’s neural activation and hormonal reactivity, and whether these differences mediate the observed changes in children’s behavioral outcomes.

**Fig. 1 Fig1:**
[figure not shown]
Overview of the most important outcomes measures, moderators and mediators of the study. *Note.* The numbers of the variables refer to the different aims of the study

**Fig. 2 Fig2:**
[figure not shown]
Flow chart of the phases through the randomized trial

## Methods/design

### Study design

The L-CID preschooler project is a 4-year randomized controlled trial. Participants are families with twins living in the western region of the Netherlands. The study consists of four assessments. Each assessment consists of a home or laboratory visit and several ambulatory assessments that are carried out by the parents at home. After two baseline assessments in year 1 and year 2, a random 40 % of the sample will receive an intervention aimed at enhancing parental sensitivity and sensitive discipline strategies of the primary caregiver, the VIPP-SD [19]. The first post-test assessment will be carried out one month after the intervention and there will be a long term follow-up two years after the intervention. This protocol paper adheres to the SPIRIT guidelines (see Additional file 1).

### Participants

#### Recruitment

Families with twins living in the western region of the Netherlands were selected from municipality records. Twins were eligible for participation if they had the same gender, if their parents were fluent in Dutch and if their parents and grandparents were born in Europe. Children with a congenital disability, psychological disorder, chronic illness, hereditary disease, or a visual or hearing impairment were excluded if the disorder will likely disable the child from performing the behavioral tasks or participating in the intervention. Also, children with a previously diagnosed intellectual disability (IQ < 70) were excluded from participation.

Eligible families (*n* = 871) received an invitation letter and information brochure by mail. Parents who were willing to participate, received a phone call during which a research assistant checked the inclusion criteria and provided additional information about the study. Families who met the inclusion criteria were then invited for the first home visit. To promote participant retention for the follow-up measures, parents will receive a financial reimbursement of €60 after home visits and €80 after laboratory visits, children will receive annual gifts and travel expenses will be compensated. In addition, participants will be informed about trial results in biannual newsletters.

#### Study sample

In total, 871 families received an invitation letter. A third of the families (37 %) did not respond to the invitation letter, 58 families (7 %) did not meet the inclusion criteria, and 271 families (31 %) did not want to participate. A final sample of 225 families (26 %) was enrolled in the study. Reasons for exclusion are shown in a flow chart (see Fig. 1). We received background information from 23 % of the eligible non-participating families. Sample characteristics from participating families and non-participating families who met the inclusion criteria are shown in Table 1. Participating families did not differ significantly from declining families on any of the background characteristics. At the time of recruitment, participating twins were on average 3.6 years old (SD = 0.57), and 50 % were boys.

**Table 1 Tab1:** Demographic characteristics of participating and non-participating families

	Participating families (*n* = 225)	Non-participating, eligible families (*n* = 131)	
Twin characteristics			
Age at recruitment M (SD)	3.60 (0.58)	3.56 (0.53)	*p* = .45
Gender (% boys)	49.8	55.0	*p* = .35
Country of birth (% Netherlands)	99.6	100.0	*p* = .45
Family characteristics			
Primary parent (%)^1^			*p* = .97
Biological mother	92.0	86.4	
Biological father	8.0	7.6	
Age primary parent M (SD)	36.81 (4.58)	37.29 (4.51)	*p* = .39
Age second parent M (SD)	38.45 (5.65)	39.52 (4.78)	*p* = .11
Country of birth (% Netherlands)			
Primary parent	95.1	92.8	*p* = .39
Second parent	96.0	92.8	*p* = .21
SES – based on parents educational level (%)			*p* = .18
Low	7.1	6.1	
Medium	39.6	49.6	
High	53.3	44.3	
Number of children in the family M (SD)	2.82 (0.78)	2.90 (1.00)	*p* = .41
Primary parents’ marital status (%)			*p* = .25
Married or registered partnership	69.2	78.6	
Cohabiting	26.8	16.8	
Single parent	3.6	4.6	
Family type (%)			*p* = .28
Biological parent(s)	98.2	96.1	
Adoptive parent	0.9	0.8	
Step parent	0.9	1.6	
Other	0.0	1.6	

^1^The percentages for the non-participating group do not sum to 100 %, because parents in seven families spend an equal amount of time with their children. The p-value is based on the values shown in the table

#### Randomization

Randomization to the VIPP-Twins or control condition is done at the family level in a ratio of 2:3, using a computer-generated blocked randomization sequence, with a block size of 19 families based on timing of the intervention and stratified by twin gender. Assignment of participants is performed by an independent researcher who is not involved in data collection or coding. Allocation will be performed after the second pretest, right before the start of the intervention, in order to prevent selective attrition. Researchers, interveners and participants are blinded to assignment before, but not after, randomization, because of the open-label design. To minimize bias based on knowledge about allocation of participants, coders and research assistants who carry out the post-intervention home-visits and laboratory sessions are blind to treatment allocation.

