### Intervention

#### VIPP-SD

The experimental group (40 % of the sample, randomly selected) will receive the Video-feedback Intervention to promote Positive Parenting and Sensitive Discipline - Twins (VIPP-Twins) between the second and third assessment. The VIPP-SD consists of five biweekly sessions in which families are visited at home by a female intervener. All interveners are extensively trained in implementing the intervention by using a standardized manual describing the structure, themes, tips, and exercises for parent and children for each session (manual VIPP-SD version 3.0; [25]). Every session starts with videotaping approximately 15 minutes of standardized parent-child interactions, such as playing or reading a book together [4]. Between sessions, the intervener prepares comments on the child’s or parent’s behavior based on the theme of the next session and selects illustrating video fragments. In the next session, after new video material is collected, the intervener reviews the video of the previous session with the parent and gives video feedback on the chosen video fragments. During this feedback period, the intervener focuses on positive and successful interaction moments and indicates when positive parenting is effective. The parent is explicitly acknowledged as the expert on her own child. The first four intervention sessions each have their own themes with respect to sensitivity and sensitive discipline [19].

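### A block of 19 families cannot hold the stated 2:3 allocation, so the article's block size and ratio do not fit together; the effect is small and the repair is cheap

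*Protocol article*

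**What the plan says.** The protocol article, under Randomization, gives the ratio and the method in one sentence: families are allocated "in a ratio of 2:3, using a computer-generated blocked randomization sequence, with a block size of 19 families", and the blocks are described as "based on timing of the intervention and stratified by twin gender".

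Two other places give the ratio as a share of the sample. Study design says that "a random 40 % of the sample will receive an intervention", and the VIPP-SD subsection under Intervention repeats it: "The experimental group (40 % of the sample, randomly selected". The sample is fixed under Study sample: "A final sample of 225 families (26 %) was enrolled in the study".

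The article does not say how the 19 families of a block are divided between the arms, or whether the division changes from block to block. It also leaves open whether 19 is a block within one twin-gender stratum or an intake batch that is then divided by gender. Under Statistical analyses, the primary model is described with condition as the between-subjects factor and time-point as the within-subjects factor. Neither timing block nor twin gender is named there.

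**The concern.** A permuted block holds a 2:3 ratio exactly only if its size is a multiple of five. Nineteen is not, so a reader cannot reconstruct the allocation sequence from what is printed. Either one of the two parameters is wrong, or a rounding rule exists that the article does not give.

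This is more than a detail left to a fuller document. The article chose to print both the ratio and the block size, and as printed they contradict each other.

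Correct description and correct analysis are at stake. Blocks are tied to the timing of the intervention. If some blocks are 7:12 and others 8:11, families entering at different times have different chances of receiving VIPP-Twins. An analysis that ignores block then mixes a small part of any cohort difference into the comparison of arms.

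**Working it through.** **Inputs from the article.** Ratio 2:3 and block size 19 (Randomization); intervention share 40% (Study design; Intervention); 225 families and 49.8% boys (Study sample, Table 1); d = 0.47, α = .05 and power above 90% (Sample size and power).

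**1. The stated share.** 2/(2 + 3) = 0.40. Over 225 families this is 225 × 0.40 = 90 intervention and 135 control. Ratio and share agree with each other.

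**2. The block.** 19 × 0.40 = 7.6, and 19 = 3 × 5 + 4. The nearest whole splits are:

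| Split of 19 | Intervention share | Intervention families if used throughout (of 225) |
|---|---|---|
| 7:12 | 7/19 = 36.8% | 225 × 7/19 = 82.9, about 83 |
| 8:11 | 8/19 = 42.1% | 225 × 8/19 = 94.7, about 95 |

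No block of 19 gives 40%.

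**3. Does stratification by twin gender remove the problem?** There are two readings.
- *Blocks of 19 within each gender.* Every block still meets 7.6.
- *Batches of 19 divided by gender.* If both parts were multiples of five, their sum would be too, and 19 is not. So at least one part of every batch cannot be split 2:3. With parts of 9 and 10, the 10 splits exactly 4:6, but the 9 would need 9 × 0.4 = 3.6.

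A rounding rule is needed on either reading.

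**4. Can the overall share still be 40%?** Yes. Two 7:12 blocks and three 8:11 blocks give (2 × 7 + 3 × 8)/(5 × 19) = 38/95 = 40%. Over the 11 full blocks that 225 families allow (11 × 19 = 209), six 8:11 blocks give (6 × 8 + 5 × 7)/209 = 83/209 = 39.7%. Seven give 84/209 = 40.2%.

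**5. Power.** This is a two-sided comparison of two means with a standardised difference of 0.47, by normal approximation: power = Φ(0.47 × √(n₁n₂/225) − 1.96). The article does not state sidedness; two-sided is assumed.

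| Intervention : control | 0.47 × √(n₁n₂/225) | Power |
|---|---|---|
| 83:142 | 3.40 | 92.5% |
| 90:135 | 3.45 | 93.2% |
| 95:130 | 3.48 | 93.6% |

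The whole range is 93.6 − 92.5 = 1.1 points. A change-score analysis with a correlation of 0.5 between assessments gives the same 93.2% at 90:135. The repeated-measures interaction calculation (f = 0.235, correlation 0.5) gives more than 99%. The article states no correlation. At an assumed 0.3, a change-score analysis at an exact 90:135 would have 83.1%, but that depends on the correlation and has nothing to do with block size.

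**6. Mixing of cohorts with arms.** Take the 3:2 mix of step 4. The 8:11 batches contribute 24 of the 38 intervention families (63.2%) and 33 of the 57 controls (57.9%), a gap of 5.3 points. If the two kinds of batch differed by an assumed 0.5 SD on the outcome, the unadjusted contrast would move by 0.5 × 0.053, about 0.026 SD. Against d = 0.47 that is 0.026/0.47, about 6% of the effect.

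**The case against.** The best defence is that the article promises 40% of the sample, not 40% of every block, and that a mix of 7:12 and 8:11 blocks delivers this. Nineteen may be an operational batch, since the block is described as "based on timing of the intervention and stratified by twin gender". An article may leave the division of a batch to the full protocol or the allocation list. If every block used the same split, the chance of intervention would be constant and cohort would not be mixed with arm at all. If the splits vary in random order, the expected shift is zero. The primary estimate is a condition-by-time interaction after two pre-allocation baselines, so stable differences in level between cohorts largely cancel. Covariates may also be set out in an analysis plan that is not shown.

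Most of this stands, and it rules out several stronger readings that a reader might infer:
- *That the randomisation cannot be carried out.* It can, with unequal splits.
- *That the overall share must move away from 40%.* Step 4 of the working shows otherwise.
- *That the trial loses its stated power.* The split changes power by about one point at most.
- *That the incomplete last block is a fault* (225 = 11 × 19 + 16). Any blocked scheme may end this way. Gender strata of about 112 and 113 families would leave a remainder with blocks of five as well.

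The defence does not remove the contradiction itself. The sentence applies the ratio and the block size to the same sequence, and no block of 19 satisfies both. Leaving a rule to another document is acceptable; printing two values that need an unstated rule to coexist is something the article should correct.

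**Conclusion.** The point holds as an inconsistency of specification with a small practical effect. Each block of 19 must depart from 40%, by 3.2 points (36.8%) or 2.1 points (42.1%) at best. Even if one split were used throughout, the trial would have about 83 or 95 intervention families instead of 90.

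Power above 90% holds under either split for d = 0.47, assuming a two-sided test and either a simple comparison of means or a repeated-measures analysis with a correlation of 0.5. Any mixing of cohort with arm arises only if the split varies between blocks. It would be about 0.026 SD under the assumed 0.5 SD difference between batch types, and less where the baselines absorb differences in level. The documents do not support calling the allocation unworkable or the arm comparison seriously confounded. A correction is still worth making because it costs almost nothing and makes the sequence reproducible.

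**What to change.** 1. **Make block size and ratio agree.** Use block sizes that are multiples of five within each twin-gender stratum. If intake batches of 19 are fixed for operational reasons, use two 7:12 and three 8:11 batches in random order per five batches (38/95 = 40%). If batches are divided by gender, also state the rounding rule for each part. The cost is a new allocation list for the cohorts not yet allocated.

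2. **Correct the Randomization section to match.** State the division of a block between the arms, whether it varies, and how blocks relate to twin gender. This costs a sentence or two.

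3. **Add timing block and twin gender to the primary model.** The trial already randomises by both. Because the estimate is a condition-by-time interaction, enter them with their interactions with time-point; otherwise they adjust the level but not the change. With about 12 timing blocks (225/19 = 11.8) this uses about 11 degrees of freedom for block and one for gender, out of 225 − 2 = 223 between families, for each contrast over time. If blocks are formed within gender, the block term already contains gender.

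4. **If allocation has begun,** keep the list as used, report the actual split in each block, and adjust for block.
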